### 3.2 Rationale for Study and Dose Selection

WinSanTor is developing pirenzepine in a topical formulation as a first-in-class topical therapy for diabetic peripheral neuropathy that not only prevents but heals the nerve damage caused by type 1 and type 2 diabetes. Pirenzepine does not have the major side effect profile expected of an M1 receptor antagonist because of its relatively poor oral bioavailability and limited blood/brain barrier penetration. Topical application of pirenzepine directly to the site affected by diabetic peripheral neuropathy is intended to maximize local concentration without significantly increasing systemic circulation, thus allowing for efficacy where needed, while minimizing the potential for systemic side effects. We have selected a topical dosage of 2 and 4 mL 4% pirenzepine (73 and 146 mg/day, respectively) based on preclinical efficacy studies and data from an exploratory clinical study with topical oxybutynin, another M1R antagonist with similar pharmacology.

## **4 STUDY OBJECTIVES**

### **4.1 Primary Objective**

The primary objective of the study is to determine the safety and tolerability of 2 dose levels of WST-057 (4% pirenzepine free base monohydrate solution) after once-daily topical administration in subjects with type 2 diabetes mellitus (T2DM) with peripheral neuropathy.

### **4.2 Secondary Objectives**

The secondary objectives of the study are:

- To evaluate the efficacy of WST-057 to increase intraepidermal nerve fiber density (IENFD) present in punch biopsies collected from the dosing area/treated skin (calf) at weeks 0 and 24 within the same subject.
- To determine the impact (defined as change from baseline) of once-daily topical dosing of WST-057 on quality of life measures using the Norfolk-QOL-DN (Total Score), Norfolk-QOL-DN Physical/Large Fiber Function, Small Fiber Function, Activities of Daily Living, and Symptoms subsets scores at week 24.

### **4.3 Exploratory Objectives**

The exploratory objective evaluated in the study is to determine the impact (defined as change from baseline) of once-daily dosing of WST-057 on quantitative thermal threshold, quantitative vibration perception, visual analogue score (VAS), the change in IENFD in an untreated location (thigh) at week 24 and the Patient's Global Impression of Change (PGIC) at week 24/EOS.

### **4.4 Pharmacodynamic Endpoints**

The following pharmacodynamic endpoints will be assessed for change from baseline:

- IENFD collected at baseline and week 24 collected from the dosing area (calf) and the nondosing area (thigh)
- Quality of life measurement (Norfolk-QOL-DN) Total Score
- Norfolk-QOL-DN Physical/Large Fiber Function subset
- Norfolk-QOL-DN Small Fiber Function subset
- Norfolk-QOL-DN Activities of Daily Living subset
- Norfolk-QOL-DN Symptoms subset
- Toronto Clinical Neuropathy Score
- Modified Toronto Clinical Neuropathy Score
- Visual Analogue Score
- Quantitative thermal threshold
- Quantitative vibration perception

- PGIC

## 4.5 Safety Endpoints

The primary safety endpoints of this study are:

- Adverse events (AE)
- Dermal Draize Score
- Clinical laboratory tests (serum chemistry, hematology, and urinalysis)
- Vital signs
- Body weight
- 12-lead electrocardiogram (ECG)
- Physical examination
- Concomitant medications

## 5 STUDY DESCRIPTION

### 5.1 Study Design

This is a randomized outpatient, double-blind, placebo-controlled, multiple-site study of the safety, tolerability, and exploratory efficacy of topically administered WST-057 (4% pirenzepine free base monohydrate) for 24 weeks in subjects with T2DM with peripheral neuropathy. Subjects will attend visits at screening (day -45 to -28); day 1 (baseline); weeks 2, 4, 8, 12, 16, 20, 24; and follow-up (week 26). Approximately 60 subjects with T2DM with peripheral neuropathy will be randomized to 1 of 4 treatment groups in a 1:1:4:4 ratio: placebo control 2 mL (n = 6 subjects), placebo control 4 mL (n = 6 subjects); low dose (2 mL) WST-057 (73 mg pirenzepine free base monohydrate) (n = 24 subjects); and high dose (4 mL) WST-057 (146 mg pirenzepine free base monohydrate) (n = 24 subjects), with the assumption that a total of 50 subjects will complete the study.

This study is designed with 4 periods: screening, baseline/day 1, outpatient treatment, and safety follow-up.

#### Screening Period (Days -45 to -28)

Subjects will be screened for eligibility during a screening period that must be completed 28 days before baseline/day 1 (ie, the screening biopsy must be taken no later than day -28 in order to allow the screening biopsy to heal). During the screening period, all necessary assessments will be performed and subject eligibility for entry into the double-blind portion of the study will be verified. Subjects who do not qualify will be discontinued and considered screen failures. If during screening, a subject fails to meet any inclusion or exclusion criteria, then the Investigator is not required to complete the remaining screening activities. The following procedures will be performed during the screening period:

- Obtain signed informed consent from the subject before any study-specific procedures are performed
- Medical history review with the subject
- Demographic information collection
- Inclusion and exclusion criteria review
- Toronto Clinical Neuropathy Score
- Modified Toronto Clinical Neuropathy Score
- Sural nerve amplitude (accepted if  $> 1 \mu\text{V}$ )
- Skin Biopsy for IENFD (accepted if  $> 1$  and  $< 10$  IENF/mm)
- Quality of Life (Norfolk-QOL-DN)
- Quantitative thermal threshold (screening)
- Quantitative vibration perception (screening)

- Dermal Draize Score (screening)
- Prior and concomitant medications review
- Complete physical examination, including height and body weight (for body mass index [BMI] calculation)
- Supine and standing vital signs
- 12-lead ECG
- Serum pregnancy test (women of childbearing potential only)
- Clinical laboratory tests
- Serology for hepatitis B surface antigen, hepatitis C antibody, and human immunodeficiency virus (HIV) 1 and 2 antibody
- Urine drug screen and alcohol breathalyzer test
- AEs
- Verify that subject is physically able to inspect lower leg, upper and lower foot for wounds, infections, or other anomalies, and will be able to self-administer the investigational drug

#### **Patient Check-in (Baseline/Day 1)**

If during the Baseline visit, a subject fails to meet any inclusion or exclusion criteria, then the Investigator is not required to complete the remaining visit activities. On the morning of day 1 (predose), the following procedures will be performed:

- Review of IENFD results from the screening calf biopsy (accepted if  $> 1$  and  $< 10$  IENF/mm)
- Verify baseline biopsy site has healed (prior to dosing phase)
- Medical history review
- Inclusion/exclusion review
- Urine drug screen and alcohol breathalyzer
- Urine dipstick pregnancy test
- Concomitant medications and AEs
- Physical examination and body weight, height, BMI calculation
- Supine and standing vital signs
- Toronto Clinical Neuropathy Score
- Modified Toronto Clinical Neuropathy Score
- 12-lead ECG
- Clinical laboratory tests (hematology, clinical chemistry, urinalysis)

- Serology for hepatitis B surface antigen, hepatitis C antibody, HIV 1 & 2 antibody
- Quantitative thermal threshold
- Quantitative vibration perception
- Visual Analogue Score
- Sural nerve testing
- Quality of Life (Norfolk-QOL-DN)
- Dermal Draize Score (baseline/day 1)
- Randomization and receipt of assigned bottle of investigative product
- Instruct subjects on the proper storage and self-administration of study drug
- Patient training on the topical application of investigational drug

### **Dosing Period (Day 2 to Week 24 $\pm$ 3 days)**

Throughout the dosing period, safety assessments will be performed and plasma samples will be collected to determine the trough concentrations of WST-057. The acceptable visit window is  $\pm$  3 days. The following additional assessments and procedures will be completed:

- Review dosing procedure (weeks 2, 4, 8, 12, 16, 20, and 24)
- Study drug dosing (day 1 to week 24)
- Physical examination and body weight, BMI calculation (weeks 2, 4, 8, 12, 16, 20, and 24)
- Vital signs (weeks 2, 4, 8, 12, 16, 20, and 24)
- 12-lead ECG (weeks 2, 4, 8, 12, 16, 20, and 24)
- Clinical laboratory tests (weeks 2, 4, 8, 12, 16, 20, and 24)
- Trough plasma sample for WST-057 pharmacokinetic (PK) analysis (weeks 2, 4, 8, 12, 16, 20, and 24)
- Quality of life (Norfolk-QOL-DN) (weeks 2, 4, 8, 12, 16, 20, and 24)
- Toronto Clinical Neuropathy Score (weeks 2, 4, 8, 12, 16, 20, and 24)
- Modified Toronto Clinical Neuropathy Score (weeks 2, 4, 8, 12, 16, 20, and 24)
- Visual Analogue Score (weekly 1-24)
- Dermal Draize Score (weeks 2, 4, 8, 12, 16, 20, and 24)
- Review of concomitant medications and AEs (weeks 2, 4, 8, 12, 16, 20, and 24)
- Dispense new bottle of assigned investigative product (weeks 4, 8, 12, 16, and 20)
- Subject is to return the remaining unused investigational drug or empty container to the Investigator (weeks 4, 8, 12, 16, 20, and 24)

### **End-of-study Procedures (Early Termination or Week 24 $\pm$ 3 days)**

- Physical examination and body weight, BMI calculation (week 24)
- Vital signs (week 24)
- 12-lead ECG (week 24)
- Clinical laboratory tests (week 24)
- Trough plasma sample for WST-057 PK analysis (week 24)
- Serum pregnancy test (women of childbearing potential) (week 24)
- Concomitant medications review (week 24)
- Adverse events review (week 24)
- Dermal Draize Score (week 24)
- Visual Analogue Score (week 24)
- Toronto Clinical Neuropathy Score (week 24)
- Modified Toronto Clinical Neuropathy Score (week 24)
- Sural nerve amplitude (week 24)
- Skin Biopsy for IENFD (week 24)
- Quality of Life (Norfolk-QOL-DN) (week 24)
- Quantitative thermal threshold (week 24)
- Quantitative vibration perception (week 24)
- Patients' Global Impression of Change (week 24)

### **Safety Follow-up (+ 10 days $\pm$ 3 days)**

Subjects who complete treatment will have a safety follow-up visit performed on week 26, during which the following assessments will be performed:

- Symptom-directed physical exam
- Concomitant medications and AEs
- Biopsy examination and suture removal, if necessary

In addition, all subjects, including those who prematurely discontinue study drug, will be contacted via telephone 28 ( $\pm$  3) days after the last dose of study drug.

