| 
* = It is acceptable to change the schedule of assessments in order to accommodate local and global health concerns and ensure patient safety due to Covid19.
 
a = The ET and EOS visits (week 24) will follow the same procedures.
 
b = Symptom directed physical examination.
 
c = Body weight and BMI calculation only. Height is taken at screening only.
 
d = Blood samples will be collected for serum chemistry and hematology, and urine will be collected for urinalysis (refer to section 7.2.2) at each visit. Subjects will be required to fast for at least 12 hours prior to collection.
 
e = For women of childbearing potential, a serum pregnancy test will be performed at screening and EOS/week 24. A urine pregnancy test will be performed at the Baseline visit.
 
f = Two standard 3-mm skin biopsies will be collected during the Screening visit from the distal leg or calf; approximately 10 cm above the malleolus and 3 cm to the posterior; and from the untreated area on the lateral thigh, approximately 25 cm below the iliac spine, approximately 5 cm below the level of the pubis and 8 cm to the posterior.
 
g = Prophylactic antibiotics may be administered to participants who, in the judgment of the Investigator, are considered to be at high risk for infection of the biopsy site.
 
h = Randomization will be prior to dose administration on day 1.
 
i = Investigational product will be administered by the subject by dispensing material from pump into palms of the hand and then spreading evenly over the calves (mid-calf sock-line), ankles and tops, and bottoms of feet.
 
j = Skin irritation (including dryness, redness, swelling, itching, burning/stinging) at the application site will be assessed using a Dermal Draize Scale prior to dosing on visit days.
 
k = Trough blood samples (1 sample at each specified visit) will be collected for pharmacokinetic analysis.
 
l = Two standard 3-mm skin biopsies will be collected during the EOS visit for early terminations or the week 24 visit. The biopsies will be collected at a distance of no less than 2 cm away and no further away than 3.5 cm from the baseline biopsy location.
 
m = The biopsy sites will be examined at the 26-week visit to monitor healing and remove sutures, if necessary. If the sutures are not suitable for removal, another visit for suture removal will be scheduled.
 
n = The visual analogue score will be collected weekly via a mobile phone application completed by the patient at the same time each week.
 |                |                |            |                |                  |                |                |                |                |                       |                 |

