#### **6.4 Withdrawal Criteria**

The subject has the right to withdraw from the study at any time.

The subject will be withdrawn from the study if 1 or more of the following occurs:

1. A deterioration in the subject's signs/symptoms and/or the subject develops a disease or condition that, in the opinion of the Investigator, would compromise the subject's safety if he/she continued in the study.
2. In the Investigator's judgment, it is in the best interest of the subject.
3. Violation of the protocol inclusion and/or exclusion criteria as deemed relevant by the Investigator and discussed with the medical monitor.
4. The subject begins to take any medication(s) that is excluded by the protocol.
5. Any of the conditions are met in [section 5.2](#), Stopping Criteria, in the judgement of the Investigator.
6. Sponsor discontinues the study.

If a subject withdraws prematurely from the trial due to the above criteria or any other reason, study staff should make every effort (at withdrawal) to complete the full set of evaluations scheduled for the final day of the treatment period. The reason for subject withdrawal must be documented in the electronic case report form (eCRF).

If a subject withdraws from the study due to an AE (eg, clinical signs, symptoms, or clinically significant laboratory abnormality), the subject will be asked, at a minimum, to return to the clinic for the evaluations scheduled for the post-treatment follow-up period. If the AE has still not resolved, additional follow-up will be performed, as appropriate, and documented in the

subject's medical records. As a minimum requirement, AEs should be followed for 30 days after the subject's last dose of study medication.

In the case of a subject lost to follow-up, attempts to contact the subject must be made and documented in the subject's medical records.

Withdrawn subjects will be replaced as needed to meet enrollment expectations.

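### Early terminators are to have the same two punch biopsies as completers, but those who stop for a reason other than an adverse event have no clearly scheduled in-person wound check

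*Protocol*

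**What the plan says.** **Who is biopsied.** Table 1 footnote a (section 5.3) equates the early-termination (ET) and end-of-study (EOS) visits: "The ET and EOS visits (week 24) will follow the same procedures". Footnote l is explicit about the biopsies: "Two standard 3-mm skin biopsies will be collected during the EOS visit for early terminations or the week 24 visit". The section 5.1 list of end-of-study procedures is headed for early termination as well as week 24 and includes the skin biopsy. For a withdrawal for any reason, section 6.4 says that "study staff should make every effort (at withdrawal) to complete the full set of evaluations scheduled for the final day of the treatment period".

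**Who has the wounds looked at.** Section 5.1, Safety Follow-up: "Subjects who complete treatment will have a safety follow-up visit performed on week 26". Biopsy examination and any suture removal are listed for that visit. The same subsection then says that "all subjects, including those who prematurely discontinue study drug, will be contacted via telephone 28" (± 3) days after the last dose. Footnote m adds: "The biopsy sites will be examined at the 26-week visit to monitor healing and remove sutures, if necessary". Section 8.3.1 lists the same examination at the week 26 visit for the subject in general.

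**Who is asked back after withdrawing.** Section 6.4, for a withdrawal due to an AE: "the subject will be asked, at a minimum, to return to the clinic for the evaluations scheduled for the post-treatment follow-up period". No matching sentence covers other withdrawals. Section 11.3, on AE follow-up, provides for re-evaluation within 2 weeks where feasible and lets minor AEs be handled by telephone.

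**The concern.** The protocol makes the same two wounds in two groups but writes the in-person healing check for one of them. Section 5.1 draws the line itself: it gives completers a clinic visit, then turns to all subjects, including premature discontinuers, and gives them a call. The subject left out is one who stops for a reason other than an AE, for example a prohibited medication, an eligibility violation or personal choice, and who agrees to the ET biopsies.

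At stake is late recognition of a poorly healing or infected site in a diabetic, neuropathic population, or a suture with no visit arranged for its removal. The self-inspection requirement in section 6.2 (criterion 9) names calves, ankles and soles but not the thigh, where the second biopsy is taken. No endpoint, estimate or test is affected. This is a point of participant care and internal consistency.

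**Working it through.** The plan gives no figure to reproduce. The check sets the clauses side by side and then sizes the group and the timing.

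**1. Is the ET biopsy really intended?** Yes. Each item in the section 5.1 end-of-study list carries a week 24 label, which alone could suggest completers only. The heading of that list, footnotes a and l, and section 6.4 remove the doubt.

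**2. Does any clause schedule an in-person site check for a non-AE early terminator?**

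| Clause | Covers this subject? | In person? | Timed from the ET biopsy? |
|---|---|---|---|
| 5.1 week 26 visit | No, completers | Yes | No |
| 5.1 telephone call | Yes | No | No, from last dose |
| Footnote m | Not excluded | Yes | No, week 26 |
| 8.3.1 week 26 visit | Not excluded | Yes | No, week 26 |
| 6.4 return to clinic | No, AE withdrawals | Yes | No |
| 11.3 re-evaluation | On a broad reading | Not necessarily | No, and no biopsy site named |
| 8.3.2 unscheduled visit | Only if a need is noticed | Yes | No |

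No row answers yes in all three columns.

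**3. Timing.**
- Completers, by the heading of the 5.1 follow-up subsection: 10 − 3 = 7 to 10 + 3 = 13 days. By the week 26 label: 26 − 24 = 2 weeks = 14 days.
- Call for early terminators: 28 − 3 = 25 to 28 + 3 = 31 days after the last dose. If the ET biopsy falls *d* days after the last dose, the call comes 25 − *d* to 31 − *d* days after the biopsy. The protocol does not give *d*. With *d* = 0 this is 25 to 31 days; with *d* = 14 (assumed) it is 11 to 17 days.
- If footnote m or 8.3.1 is applied literally to an early terminator biopsied at, say, week 8, the check comes 26 − 8 = 18 weeks later.

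**4. Benchmark within the protocol.** The screening biopsies are taken between day −45 and day −28 (section 5.1). Table 1 has no visit between screening and day 1, and the first listed healing check is on day 1. Every subject therefore already goes about 28 days or more without a scheduled clinic check of the same kind of wound.

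**5. Number affected.** Randomised 60, assumed completers 50 (sections 5.1 and 6.1): 60 − 50 = 10 planned non-completers, and 10/60 = 16.7%. Neither the share who stop for a non-AE reason nor the share who accept the biopsy is given. Letting their product run over its whole range, 0 to 1, gives 0 to 10 subjects and, at two biopsies each, 0 to 20 sites. Section 6.4 lets withdrawn subjects be replaced, so the number of non-completers can exceed 10.

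**The case against.** The strongest reply is that other sections already cover most of this. Section 8.3.1 sets out its visits for each subject and does not limit the week 26 biopsy examination to completers. Footnote m is likewise unrestricted and allows a further visit if sutures cannot yet come out. Section 11.3 can be parsed so that any withdrawal, with or without an AE, triggers re-evaluation within 2 weeks. A wound complication would itself be an AE with its own follow-up, and section 8.3.2 permits unscheduled visits. Section 7.1.1 also leaves biopsy details to a separate procedure document for sites, which may contain aftercare instructions and is not available to check.

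Much of this stands, and it is why the point says only that no check is *clearly* scheduled. A reader might infer that early terminators are left with no wound follow-up at all. The documents do not support that, because these clauses give a site several routes to see the subject. What they do not do is fix an in-person examination at a set time after an ET biopsy. The week 26 anchor does not work for someone who stopped early, section 11.3 is conditional and does not mention the biopsy site, and an unscheduled visit needs someone to notice a problem first.

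The second reply concerns seriousness, and it stands. Section 7.1.1 describes a biopsy 3 to 4 mm deep that should need no suture. Foot ulcers and severe immunocompromise are exclusions, and footnote g allows prophylactic antibiotics. The protocol also accepts a similar interval after screening. A reader might infer a major safety hazard; the text does not bear that out.

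**Conclusion.** The point holds as a minor safety and consistency gap. Section 5.1 restricts the post-biopsy clinic visit to completers, while early terminators are to have the same two biopsies. For those who stop for a non-AE reason, no other clause clearly schedules an in-person check of the sites. The restriction is stated in the text, so it is more than detail left to another document.

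The number of subjects is small and unknown. The planning figure of 10 non-completers should not be read as an upper bound, since withdrawals may be replaced. No narrower range can be drawn without assuming both the non-AE share and the biopsy acceptance rate. The risk per wound is low. The case for acting rests on how little the correction costs, not on the size of the hazard. The one thing that could make it unnecessary is aftercare wording in the site procedure document, and even then section 5.1 would still need to agree with it.

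**What to change.** - In section 5.1, give the follow-up visit to all subjects who complete treatment or who have EOS or ET biopsies. Naming both groups keeps the visit for a completer who declines the biopsy.
- Set the in-clinic site check, with suture removal if needed, at 10 ± 3 days after the EOS or ET biopsy, whatever the reason for stopping. This also settles the difference between the 7 to 13 days in the subsection heading and the 14 days implied by week 26.
- Word footnote m and section 8.3.1 the same way.
- Keep the 28-day telephone call in addition.

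The cost is wording edits in three places and one short clinic visit for each biopsied subject who stops for a reason other than an AE. AE withdrawals are already asked to return, so they add nothing new. The downside is the added visit for subjects who have chosen to leave, some of whom will decline it.

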## **5.2 Stopping Criteria**

Dose administration will be discontinued immediately according to the following criteria.

